### Recruitment {15}

Both recruitment site hospitals have a database of children with ASD, which will be available to the research team to identify potential participants, with support of a referring clinician at the recruitment site. Enrolment of new cases registering with both sites will also be undertaken. Our planned recruitment rate of 17/month overall will be well within this total of newly registered and historic cases. Families will be initially identified and informed by referring clinicians at recruitments sites who will be supported by COMPASS RAs or project appointed recruitments officers. On agreement this team of clinicians, RAs and recruitment officers will assess geographical eligibility and proceed with informed consent. Each case will be registered and assigned a unique referral ID number.

### Data management {19}

All trial data will be anonymised. A central master file will be held by the trial director at Sangath. This will contain the key linking anonymised participant IDs to personal details.

COMPASS uses multiple platforms across various institutions for trial data management and randomisation. Details of these are as below:REDCap: This is a secure web application for building and managing online surveys and databases. Whilst REDCap can be used to collect virtually any type of data in any environment (including compliance with 21 CFR Part 11, FISMA, HIPAA, and GDPR), it is specifically geared to support online and offline data capture for research studies and operations.REDCap Cloud (RCC): This aggregates real-world data in a standard way and mines it to make unbiased and data-driven discoveries on clinical trials. The RCC helps the clinical trial unit (CTU) at the University of Manchester and Sangath, India (COMPASS Trial Team), to transfer, integrate and monitor data quality.COMPASS Archival Unit (AU): This sub-team of evaluation team members collects, runs quality checks and systematically stores all data collected using paper forms.King’s Clinical Trials Unit (KCTU): The KCTU manages a bespoke online randomisation system, supporting simple randomisation, block randomisation, stratified block randomisation and minimisation. The COMPASS uses KCTU services for randomisation of participants in the trial into the treatment as usual (TAU) group or PASS-Plus + TAU group.

## Assignment of interventions: allocation

### Sequence generation {16a}

Children will be assessed for eligibility using the following: (1) the INCLEN Diagnostic Tool-ASD (INDT-ASD) to confirm the ASD diagnosis and (2) the Mullen Scales of Early Learning [25] to confirm a level of non-verbal development of 13 months or more. As mentioned above, we will use the motor skill domain of Vineland 3 for ascertaining eligibility in terms of age equivalence as a replacement for Mullen Scales of Early Learning as an adaptation to the COVID-19-related restrictions. RAs will then undertake baseline assessment with all consented and eligible participants prior to treatment assignment. Randomisation will be conducted through the King’s Clinical Trials Unit web-based randomisation service. Allocation will be by minimisation, controlling for age strata (2–4 years, 5–9 years) and centre (AIIMS, MAMC-LNH). Randomisation confirmation will be emailed to the trial director in India and to the CTU and treatment allocation will be emailed to the intervention supervisors/coordinators by the trial director.

### Allocation concealment mechanism {16b}

As randomisation will be performed through an independent service at KCTU, the allocation sequence will be concealed until participants are assigned allocations.

### Implementation {16c}

Participants will be recruited and consented into the trial by COMPASS RAs. Eligibility and baseline assessments will be conducted before treatment assignment. Participants will be assigned to one particular randomisation batch. The list of participants for each batch will be sent through to the trial director who will carry out the randomisation. Unblinded treatment allocation emails will be sent to the intervention coordinators. They will then contact each participant via phone call informing them of their allocation. Participants allocated to the intervention group will be invited to the sessions.

## Assignment of interventions: blinding

### Who will be blinded {17a}

Research and statistical staff will be blinded to treatment allocation; therapists, families and parent-rated secondary outcomes cannot be blinded. Primary and researcher rated secondary outcomes will be done by video-coding, by trained coders blind to allocation.

### Procedure for unblinding if needed {17b}

All analysis will be pre-specified and the trial dataset will be generated with a dummy variable for group allocation, and the primary analysis will be conducted prior to unblinding group identities.

## Data collection and management

### Plans for assessment and collection of outcomes {18a}

The primary endpoint will be at 9 months after randomisation, with a follow-up assessment at 15 months with specific COVID-19-related adaptations as mentioned above. Baseline, endpoint and follow-up data will be collected by RAs during home and centre visits. All data will be collected in accordance with trial standard operating procedures. Data for the majority of measures will be captured directly onto a tablet database using REDCap; some data will be collected in paper format if difficult to collect and/or score in REDCap. Data collected using paper forms will be entered directly into the Redcap Cloud (RCC) database.

Following are the four types of processes followed for data management.

#### Type 1

In this, data will be directly collected on REDCap by RAs. The evaluation measures in the type 1 are as follows: PIS, demographics questionnaire, COVID-19 Impact Questionnaire, adverse events form, DBC-P, WEMWBS, PEDS-QL and CHU-9D. Once entered in REDCap, the data will then be uploaded to RCC by a data entry operator (DEO).

#### Type 2

Data for these evaluation measures will be collected on paper forms. The evaluation measures in type 2 are as follows: consent form, INDT-ASD, CSBS-DP, EQ-5D and Vineland-3. The data collected on the consent form and the summary scores of INDT-ASD are entered by the RA on REDCap, whilst data for CSBS-DP and EQ-5D is entered by a DEO. A separate process will be followed for Vineland-3, wherein RAs enter data in Q-global, which further provides domain summary scores. These summary scores will then be entered in REDCap by the DEO. All data will finally be transferred from REDCap to RCC. Post the data entry, paper forms will be submitted back to an archival unit (AU) for systematic and safe storage.

#### Type 3

The only evaluation measure in this type will be the COII. The data will be collected on the paper form by RAs and then submitted to the AU. Upon submission, AU will run the required quality check and then hands over form(s) to the DEO for data entry. The data will be directly entered into RCC by DEO.

#### Type 4

The type 4 includes all video and digital assessments, viz., BOSCC, DCMA, and START. The BOSCC and DCMA videos will be shot and stored in the electronic tablet during centre visit. Post centre visit RAs will submit the videos to AU where a quality check of the videos is done by DEO. Once the videos clear the quality check, they will be uploaded on REDCap and thereon to RCC by DEO, post which assessors will be given the permission to permanently delete the videos from their respective tablets.

Appropriate quality control will be carried out during the trial and before the database lock. Primary analysis of the data will take place by the trial statisticians and chief investigator. Other members of the team will also have access to data and will undertake analysis as appropriate and necessary.

### Plans to promote participant retention and complete follow-up {18b}

This trial will require a significant time commitment from families. Each trial family will need to be visited five to seven times over the course of data collection. Some of these visits will be organised at participant homes to minimise inconvenience to families. In recognition and appreciation of this time commitment, all families will receive a participation token of INR 500 on completion of eligibility assessments whether or not they are eligible for the trial. INR 1000 will be provided on completion of assessments at each assessment timepoint, i.e. baseline, endline and follow-up. This will be a total of INR 3500 for each participant across the course of the trial.

On successful completion of the Vineland-3, an assessment feedback report compiled by the research team, detailing adaptive skills, will be provided to all trial participants at baseline and 15-month follow-up assessment time points. This report will also include the age equivalence of the different sub-domains of adaptive skills, viz, communication, daily living, socialisation and motor skills. Periodic newsletters and customised birthday cards will be also sent out all participants through the duration of the trial to promote engagement of participating families.

Furthermore, conducting assessments at endline and follow-up with participants will need concerted efforts by the evaluation team. Hence, information about participants who are non-contactable over telephone calls will be shared with respective recruitment sites so that they can contact the participants and check their willingness to continue participation in the trial. In the event that the recruitment sites are unable to get in touch with them, a visit to participant’s household by a designated COMPASS evaluation team member/assessor will be planned in order to enquire about participant’s willingness to continue and address any concerns that may have. This will be considered as the last attempt, following which, if the participant refuses, they will be considered as having withdrawn consent or, if still non-responsive, then lost to follow-up for relevant reasons.

### Confidentiality {27}

Data protection and confidentiality procedures will be specified and followed, in keeping with Good Clinical Practice and the General Data Protection Regulation 2018. All video recordings will be made only after written consent has been obtained from parents. Video recordings will be viewed only by members of the COMPASS team and for the purposes of the research and therapy, unless further explicit written consent is obtained. All video and audio recordings will be held securely in a locked cabinet on an encrypted hard-drive and will be shared only via a secure server system hosted in the University of Manchester and in accordance with pre-specified highly secure procedures. All data will be kept confidential, accessed only by the trial team. Personal information may be shared only with parental consent, e.g. with clinicians involved with the family. The only time that personal information will be shared without parental consent is if there are serious concerns about the safety or wellbeing of a child or vulnerable adult. In this event, local procedures for safeguarding children and vulnerable adults will be followed. Electronic and paper-based data collection forms will be identifiable only by participant ID and will contain no names or contact details. Personal and sensitive data will be stored separately and securely in an encrypted form, on a password-protected hard drive or computer in a secure office. If personal information needs to be emailed, this will be in an encrypted form.

## Statistical methods

### Statistical methods for primary and secondary outcomes {20a}

All statistical analysis will be undertaken after the 15-month outcome measures are completed. All analyses will be carried out using the most recent version of Stata [26]. In accordance with CONSORT Statement for Social and Psychological Interventions (2018), we will report all participant flow through the trial. Additionally, we will follow the CONSORT and SPIRIT Extension for RCTs Revised in Extenuating Circumstances (CONSERVE) statement for reporting the results of the trial [27]. Descriptive statistics of recruitment, drop-out and completeness of interventions will be provided. The main efficacy analysis will be via intention-to-treat including all participants, with no planned interim analysis for efficacy or futility. Baseline characteristics will be presented by randomised group without formal statistical tests.

We will test the primary hypothesis for between-group difference in the primary outcome (BOSCC) using generalised linear mixed models allowing for clustering by participants and therapists with fixed effects including baseline outcome measure, centre, age-group stratifier, treatment assignment, time (treated as a categorical variable) and time * treatment interaction. We will explore potential moderating effects by baseline severity, co-morbidities, home environment and parental education including interactions between the moderator and randomisation. Marginal treatment effects will be estimated for outcomes at each time point and reported separately as adjusted mean differences in scores between the randomised groups with 95% confidence intervals and two-sided *p*-values. The secondary outcomes will be analysed using an analogous method.

The analysis will use statistical techniques for handling missing outcome data under a missing at random assumption and simple mean imputation for missing baseline measures.

As a secondary exploratory analysis, we will estimate the effect of each additional adequate therapy session using instrumental variable regression, the model being identified by assuming an exclusion restriction of the form that the offer of treatment does not of itself influence the outcome, once receipt of treatment has been accounted for.

For the mediation analysis, if the efficacy analysis shows significant between group differences in the mediator (DCMA), then we will use parametric regression models to test for mediation of the intervention on BOSCC outcomes through DCMA. Since all the measures are continuous, the indirect effects are calculated by multiplying relevant pathways and bootstrapping is used to produce valid standard errors for the indirect effects. Mediation analyses are potentially biased by measurement error in mediators and hidden confounding between mediators and outcomes; we will build on our previous methodological and applied work in this context to include repeated measurement of mediators and outcomes to account for classical measurement error and baseline confounding.

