#### Trial update as on March 2023

The COMPASS trial completed randomisation of 261 participants on 16 December 2022. As of 31 March 2023, 157 (60%) endpoint assessments were completed and 30 participants (11.5%) were lost to follow-up. Also, 86 (33%) follow-up assessments (15 months post randomisation) were completed by the end of March 2023.

Adaptation to the assessment processes were made during the COVID-19 pandemic-related restrictions (these are detailed the above section). It has taken relatively more time to complete the telephonic assessments compared to in-person contacts. Telephonic assessments take between 4 and 6 contacts with each participating family; every contact takes around 60 min and an additional in-person contact for BOSCC, DCMA and START administration. In-person assessments are completed in 3 contacts, each ranging from 60 to 90 min. In both cases, the number of contacts and the time duration can vary depending on the family’s need and availability. However, it is also important to note that the method of administration of the primary trial outcome, i.e. the BOSCC has remained same throughout the trial (Table 1).

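### Continuous measures do not by themselves justify multiplying paths: the product is the indirect effect only if the DCMA-to-BOSCC slope is the same in both arms

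*Protocol article*

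**What the plan says.** The mediation paragraph in Statistical methods for primary and secondary outcomes {20a} is triggered only if DCMA differs significantly between the groups. In that case "we will use parametric regression models to test for mediation of the intervention on BOSCC outcomes through DCMA". The estimator and the reason for it come in one sentence: "Since all the measures are continuous, the indirect effects are calculated by multiplying relevant pathways", with bootstrap standard errors.

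The paragraph then names two sources of bias: "Mediation analyses are potentially biased by measurement error in mediators and hidden confounding between mediators and outcomes". Its remedy is to "include repeated measurement of mediators and outcomes to account for classical measurement error and baseline confounding". It does not mention a slope that differs by arm, and it neither includes nor excludes an allocation x DCMA term. It also does not say which wave's DCMA is paired with which wave's BOSCC.

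On timing, Plans for assessment and collection of outcomes {18a} states: "The primary endpoint will be at 9 months after randomisation, with a follow-up assessment at 15 months". Under Type 4 of the same section, "The BOSCC and DCMA videos will be shot and stored in the electronic tablet during centre visit". The March 2023 trial update says that the telephone schedule needs "an additional in-person contact for BOSCC, DCMA and START administration". Adapting assessment timepoints keeps the endline and follow-up assessments at least 3 months apart.

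**The concern.** Continuity of mediator and outcome allows linear models for both. It does not make the product of the two coefficients equal the indirect effect. For that, the outcome model must also have no treatment-by-mediator interaction. If the slope differs by arm, there are two natural indirect effects: the pure one, which uses the TAU slope, and the total one, which uses the intervention slope. A model without the interaction averages the two slopes, so its product is neither effect. The bootstrap then gives an interval around that average and does not change what is being estimated.

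Time order is a second, smaller matter. DCMA and BOSCC can be recorded at the same contact. If the mediation model paired them within a wave, it could not tell whether a better dyad lowers symptoms or milder symptoms make a better dyad. The repeated measures are assigned to measurement error and baseline confounding, not to this.

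What is at stake is the reading of mechanism. The article's introduction presents change in parent–child communication as the route by which the parent therapy worked in the UK, and a mediation result here would be read as a test of that theory.

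**Working it through.** The article states no figure for the mediation analysis, so there is none to reproduce.

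**Inputs.** From the article: product of paths, roughly equal allocation, and waves at baseline, 9 and 15 months. Not in the article, so assumed: a DCMA shift of a = 1 SD, an average slope of -0.3, a slope gap from 0 to 0.6, and an SD ratio between arms from 0.67 to 2.

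**Formulas.** Let T be allocation, M be DCMA and Y be BOSCC. The slope of Y on M is b0 under TAU and b1 under intervention, and the SD of M is s0 and s1.

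- Pure natural indirect effect = a × b0
- Total natural indirect effect = a × b1
- Product without the interaction, 1:1 allocation = a × (s0²·b0 + s1²·b1) / (s0² + s1²)

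**Equal SDs (s0 = s1 = 1).** The product is a × (b0 + b1)/2.

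| b0 / b1 | Product | Pure | Total | Product against total |
|---|---|---|---|---|
| -0.3 / -0.3 | -0.30 | -0.30 | -0.30 | equal |
| -0.2 / -0.4 | -0.30 | -0.20 | -0.40 | 25% short |
| -0.1 / -0.5 | -0.30 | -0.10 | -0.50 | 40% short |
| 0 / -0.6 | -0.30 | 0.00 | -0.60 | 50% short |

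A least-squares simulation with 400,000 participants gave the same values to within 0.01.

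**Unequal SDs, slopes -0.1/-0.5.** The pure and total effects stay at -0.10 and -0.50, but the product moves:

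- s0 = 1, s1 = 1.5: (-0.1 - 2.25 × 0.5)/3.25 = -0.38
- s0 = 1, s1 = 2: (-0.1 - 4 × 0.5)/5 = -0.42
- s0 = 1.5, s1 = 1: (-2.25 × 0.1 - 0.5)/3.25 = -0.22

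So when slopes differ, the product also depends on the spread of DCMA in each arm.

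**Time order, if the pairing is within a wave.** Take a scenario with a true indirect effect of zero: Y = -0.45·T + noise, then M = -0.4·Y + 0.5·T + noise, with unit noise SDs.

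- Path from T to M: 0.5 + 0.4 × 0.45 = 0.68
- Slope of Y on M given T: -0.4/(0.16 + 1) = -0.345
- Product: 0.68 × (-0.345) = -0.23 (simulation -0.24), about half of the total effect of -0.45, and all of it spurious

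Now let 15-month BOSCC be 0.7 times 9-month BOSCC plus noise. Using 9-month DCMA with 15-month BOSCC but without 9-month BOSCC gives 0.7 × (-0.23) = -0.16, still spurious. Adding 9-month BOSCC as a covariate gives 0.00.

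**The case against.** The strongest reply is that interaction terms and wave pairing are details for an analysis plan that is not shown, and that a condensed article may leave them out. That stands for the omissions: neither is an error in itself. It does not cover the stated reason, because the article fixes the estimator and justifies it by continuity alone.

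It can also be said that nothing shows the slopes to differ. That stands too. A reader might infer a difference from the fact that the therapy trains parents in behaviour that DCMA scores. That explains a large allocation-to-DCMA path; it may make an unequal slope plausible, but it does not establish one. Nor can the bias be put in BOSCC points. The pilot shift of 0.35 in parent synchrony is available, but no DCMA-to-BOSCC slope is, and an assumed slope can easily imply an indirect effect larger than the whole 5-point target.

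A reader might further infer that the planned analysis uses same-contact measurements, so that direction cannot be shown. The documents do not support this. The passages on filming describe logistics, the mediation paragraph fixes no pairing and plans repeated measures of both variables, and the two later waves allow a lagged model.

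Finally, mediation is not among the listed objectives, runs only if DCMA differs significantly, and is presented with an open warning about bias. That limits the severity.

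**Conclusion.** The point holds in a limited form. The rationale for multiplying paths is incomplete, because equal slopes in the two arms are needed as well as continuous measures. The size of any error is unknown. It is nil with equal slopes. On the assumed slope gaps of 0.2 to 0.6, with equal SDs and a 1 SD shift, the product falls 25% to 50% short of the total indirect effect and overstates the pure one by 0.10 to 0.30. These figures rest on linear models and invented slopes, and they illustrate rather than predict. The concern about direction applies only if DCMA and BOSCC are paired within a wave, which the article does not say. Severity is minor: neither the primary test nor the cost-effectiveness analysis depends on this.

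**What to change.** - Replace the continuity rationale with the assumption the product needs: no allocation x DCMA interaction in the BOSCC model.
- Fit the outcome model with that term and report natural direct and indirect effects (pure and total) with bootstrap intervals, beside the product estimate. They coincide when the interaction is zero, so nothing is lost if the slopes are equal.
- State which wave's DCMA is paired with which wave's BOSCC.
- As a supportive analysis only, relate 9-month DCMA to 15-month BOSCC, adjusting for baseline DCMA and for baseline and 9-month BOSCC. Without 9-month BOSCC the lag keeps part of the reverse-direction bias. The model speaks to effects after 9 months, away from the primary endpoint, so it should not replace the main mediation model.

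The cost is analysis wording and a few more models. Both later waves are already planned, so no new data collection is needed. Expect wider intervals from the interaction term and some loss of cases at 15 months. None of this removes hidden confounding between mediator and outcome, so the article's own caution on that should stay.
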